**Success rate of diagnostic cerebral angiography**

Successful diagnostic angiography: the aortic arch vessel is successfully selected without changing the puncture site, with angiography results meeting the diagnostic requirements.

For intraoperative management, please refers to *Chinese Expert Consensus on Good Practice for Cerebral Angiography (2018)*.

In case of angiography failure, record in which of the following stages it occurs and why it occurs:

Stage 1: Unable to insert the arterial sheath (small artery diameter, no blood return after arterial puncture, unable to advance the guidewire due to vasospasm, and atherosclerotic plaque, etc.);

Stage 2: Puncture and sheath placement is successful, but the catheter or guidewire cannot be advanced (arterial tortuosity, vasospasm, and loop, etc.);

Stage 3: The guidewire and catheter has reached the aortic arch, but the primary branch of the aortic arch cannot be selected;

Stage 4: The guidewire and catheter has reached the primary branch of the aortic arch, but the procedure still cannot be completed successfully;

➤ **Secondary Effectiveness Endpoints:**

- Success rate of accurate diagnosis: successful accurate diagnosis is defined as the responsible vessel for the disease is successfully superselected without changing the puncture site, with angiography results meeting the diagnostic requirements.
- Duration of angiography: Time from puncture to the end of the angiography.
- Duration of fluoroscopy: Data from the machine will be used.
- Bedridden time: Time (hours) from the end of the procedure to ambulation.
- Visual Analogue Scale (VAS) score: The VAS will be completed within 24 hours after the end of the angiography. The VAS is provided in Appendix 3.

(2) Safety Endpoints:

- Incidences of angiographic complications during and within 24 hours after the procedure
- Incidences of major angiographic complications during and within 24 hours after the procedure

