| To analyze factors affecting cerebral angiography via TRA approach.                                                                                         | 
 
• Clinical and imaging data (age, diabetes, hypertension, hyperlipidemia, smoking history, Type III aortic arch configuration, looping technique, diameter and development status of the radial artery, development status of the aortic arch and the vessels above the arch and degree of tortuosity, previous operation history especially of the radial artery) of all patients undergoing TRA cerebral angiography will be investigated, to analyze the factors affecting TRA cerebral angiography.
 
 |

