## 5. Analysis Sets

| Population              | Definition / Criteria                                                                                                                                                                     | Analyses Evaluated                                                                      |
|-------------------------|-------------------------------------------------------------------------------------------------------------------------------------------------------------------------------------------|-----------------------------------------------------------------------------------------|
| Full Analysis Set (FAS) | 
 
The FAS will include subjects randomized to receive TRA or TFA cerebral angiography, with recorded evaluation results of the diagnosis.
 
 | 
 
Population analyses
 
Efficacy
 
 |

| Population             | Definition / Criteria                                                                                                                                                                                                                                                                                                                                                                                                                                                                                                                                                                      | Analyses Evaluated                                         |
|------------------------|--------------------------------------------------------------------------------------------------------------------------------------------------------------------------------------------------------------------------------------------------------------------------------------------------------------------------------------------------------------------------------------------------------------------------------------------------------------------------------------------------------------------------------------------------------------------------------------------|------------------------------------------------------------|

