|                        | 
 
Statistical analysis will be performed according to the intervention group randomly assigned (regardless of the actual intervention received).
 
The FAS is the main set for the efficacy analysis of this study.
 
                                                                                                                                                                                                                                                                                                                 |                                                            |
| Safety Set (SS)        | 
 
The SS will include all subjects randomized and received cerebral angiography via TRA approach or TFA approach.
 
This analysis will be performed according to the actual intervention received.
 
                                                                                                                                                                                                                                                                                                                                  | 
 
Safety
 
   |
| Per Protocol Set (PPS) | 
 
PPS is a subset of the FAS, including subjects from the FAS with no major protocol deviations.
 
The criteria for major protocol deviations should be finalized before the lock of the database, and the lists of subjects to be included and excluded from the PPS should be reviewed and discussed by the principal investigator, the statistician, and the sponsor at the data review meeting before the lock of the database.
 
PPS-based analyses will serve as supportive analyses to complement FAS-based analyses.
 
 | 
 
Efficacy
 
 |

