## 8.1.2. Specifications of Primary Efficacy Endpoint(s) Analyses

### 8.1.2.1. Definitions and Derivations

The primary effectiveness endpoint of this study is the rate of successful diagnostic cerebral angiography, which is defined as the aortic arch vessel is successfully superselected without changing the puncture site, with angiography results meeting the diagnostic requirements. Any change of puncture site before or during the procedure after a subject has been randomized would be treated as a diagnosis failure.

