### 8.1.2.2. Analysis Methods

#### 8.1.2.2.1. Overview of Analysis Methods

| Analysis                | Analysis Set | Statistical Analysis Methods                                                                                                                                                                 | Handling of Missing Data                             |
|-------------------------|--------------|----------------------------------------------------------------------------------------------------------------------------------------------------------------------------------------------|------------------------------------------------------|
| Primary Endpoint |              |                                                                                                                                                                                              |                                                      |
| Primary analysis        | FAS          | Normal approximation method for calculating 95% CI of rates;
Normal approximation method for calculating 95% CI of difference in rates;
Wald Z test;
Generalized linear regression. | Missing primary outcome will not be included in FAS. |
| Supplementary analysis  | PPS          | Same as primary analysis.                                                                                                                                                                    | Missing primary outcome will not be included in PPS. |

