## 10. Exploratory Analyses

### 10.1. Overview of Planned Exploratory Endpoints Analyses

The exploratory endpoints analyses will be based on the TRA group population in the FAS, unless otherwise specified.

Table 7 provides an overview of the planned exploratory endpoints analyses.

|                                                           |                          |
|-----------------------------------------------------------|--------------------------|
| QMS Document Name: Statistical Analysis Plan Template(EN) | Page 28 of 38            |
| QMS No (include version ref): STF-015-GL.03               | Document date: 14JUL2022 |
| CONFIDENTIAL                                              |                          |

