### 10.2.3. Model Specifications

| Statistical Analysis of Exploratory Variables                                                                                                                                                                         |                          |
|-----------------------------------------------------------------------------------------------------------------------------------------------------------------------------------------------------------------------|--------------------------|
| Endpoints and Parameters                                                                                                                                                                                              |                          |
| 
 
• Endpoints: successful/ failed cerebral angiography through TRA approach
 
• Parameters: 
 
– RR and 95% CI
 
 
 
 |                          |
| Input Variables                                                                                                                                                                                                       |                          |
| 
 
• AVAL: Response variable
 
• COVARIATES: Influencing factors
 
                                                                                                |                          |
| Sample SAS code                                                                                                                                                                                                       |                          |
| 
Generalized linear regression sample code:
 <pre>PROC GENMOD DATA=adeff;   CLASS TRTPN;   MODEL AVAL = COVARIATES / DIST=BIN LINK=LOG   SELECTION=STEPWISE;   RR COVARIATES / CL;</pre>                  |                          |
| QMS Document Name: Statistical Analysis Plan Template(EN)                                                                                                                                                             | Page 30 of 38            |
| QMS No (include version ref): STF-015-GL.03                                                                                                                                                                           | Document date: 14JUL2022 |

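### The exploratory TRA-factor model counts TRA-assigned subjects with no radial attempt as TRA failures, although its objective concerns patients undergoing TRA (minor)

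*Combined protocol and SAP*

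**What the plan says.** - **Question.** SAP 1.2 says that clinical and imaging data "of all patients undergoing TRA cerebral angiography will be investigated, to analyze the factors affecting TRA cerebral angiography". Protocol 3.2 names the same population.
- **Outcome.** SAP 10.2.3: "Endpoints: successful/ failed cerebral angiography through TRA approach".
- **Population.** SAP 10.1: "The exploratory endpoints analyses will be based on the TRA group population in the FAS, unless otherwise specified". Section 10 never takes up the closing reservation: it names no other set and no sensitivity analysis.
- **Grouping.** SAP 5, on the FAS: "Statistical analysis will be performed according to the intervention group randomly assigned (regardless of the actual intervention received".
- **Membership.** SAP 5: "The FAS will include subjects randomized to receive TRA or TFA cerebral angiography, with recorded evaluation results of the diagnosis". SAP 8.1.2.2.1 adds: "Missing primary outcome will not be included in FAS".
- **Failure rule.** SAP 8.1.2.1, with the same rule in protocol 7.7.1: "Any change of puncture site before or during the procedure after a subject has been randomized would be treated as a diagnosis failure".
- **Failure stages.** Protocol 2.2 records four stages, beginning with "Stage 1: Unable to insert the arterial sheath".

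**The concern.** The factor model is meant to show which patient and vessel features make radial angiography fail. Under the rules above, a subject sent directly to femoral access after allocation to TRA enters the model as a failure of a route that was never tried. Such a switch can have causes unrelated to the vessel, or it can be prompted by one of the candidate factors, for example earlier surgery on the radial artery.

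Failures are expected to be few, so a handful of these subjects could change what the model explains. Protocol 2.1 lists this question as its only secondary objective, although protocol 7.7.3 and SAP 1.2 both treat it as exploratory.

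**Working it through.** **1. How each kind of subject is handled**

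| Subject | In the factor model? | Scored as | TRA attempted? |
|---|---|---|---|
| TRA arm, radial angiography completed and diagnostic | yes | success | yes |
| TRA arm, radial attempt fails at stage 1-4 | yes | failure | yes |
| TRA arm, femoral access without a radial attempt, evaluation recorded | yes | failure | no |
| TRA arm, no recorded evaluation | no | - | - |
| TFA arm, converted to TRA | no | - | yes |

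The third row is the problem. The fifth is the reverse mismatch: these subjects underwent TRA but are left out. All four stages in protocol 2.2 presuppose an attempt, so a third-row subject has no stage.

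**2. Expected number of failures**

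SAP 3 gives success rates of 97% (TRA) and 98% (TFA), a margin of -5%, one-sided alpha of 0.025, 90% power, 10% drop-out and 429 per group. The 429 can be reproduced. With exact binomial power for a continuity-corrected pooled Z test, 386 is the first n per group to reach 90% (power 0.9050; 0.8992 at 385), and 386 / 0.9 = 428.9, which rounds up to 429.

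Expected TRA failures are 0.03 x 386 = 11.6 among evaluable subjects, or 0.03 x 429 = 12.9 with no drop-out.

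**3. Share of modelled failures that are pre-puncture switches**

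The number of switches, k, is not in the documents and is assumed here. With a 3% failure rate among attempts, the share is k / [k + 0.03 x (386 - k)]:

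- k = 2: 2 / (2 + 11.52) = 15%
- k = 4: 4 / (4 + 11.46) = 26%
- k = 6: 6 / (6 + 11.40) = 34%
- k = 12: 12 / (12 + 11.22) = 52%

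If the planned 3% already includes such switches, each one is 1 / 11.6, or about 9% of the failures.

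**4. Switching unrelated to the factor**

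Assume a factor with 20% prevalence, a true failure risk ratio of 3.0 and 3% failure overall. Failure in the unexposed is pu = 0.03 / (0.8 + 0.2 x 3) = 0.0214, and in the exposed pe = 0.0643. With switch rate s, the observed failure ratio is [pe(1 - s) + s] / [pu(1 - s) + s]:

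- s = 0.5%: 0.0690 / 0.0263 = 2.62
- s = 1%: 0.0736 / 0.0312 = 2.36
- s = 2%: 0.0830 / 0.0410 = 2.02

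For success, the factor (1 - s) cancels: (1 - pe) / (1 - pu) = 0.9357 / 0.9786 = 0.956 at every s.

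**5. Switching related to the factor**

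Assume a factor with no effect (3% failure everywhere), 20% prevalence, and switches in 1% of the arm that all fall among the exposed. The switch rate in the exposed is 0.01 / 0.20 = 5%, so their failure rate is 0.03 x 0.95 + 0.05 = 7.85%. The failure ratio becomes 7.85 / 3 = 2.6 and the success ratio 0.9215 / 0.97 = 0.95. Both should be 1.

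**6. Sampling error for scale**

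With 386 subjects and the step 4 assumptions, there are 4.96 failures among 77.2 exposed and 6.62 among 308.8 unexposed. SE(log RR) = sqrt(1/4.96 - 1/77.2 + 1/6.62 - 1/308.8) = 0.58, so the 95% interval for a ratio of 3.0 is about 0.96 to 9.35.

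**The case against.** **The group may be empty.** No switch rate is documented. Protocol 4.1 and 4.2 require suitability for both routes and a radial diameter of at least 2 mm, and exclude severe access-path stenosis. Appendix 1 places randomisation and procedure at one visit. This stands as a limit on size. It does not remove the gap: the plan writes a rule for changes before the procedure, and Appendix 1 accepts vessel imaging from up to 90 days before consent.

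**Sampling error dominates.** A move from 3.0 to 2.4 is small beside an interval of 0.96 to 9.35, in a model planned only if data permit (SAP 10.2.2). This stands and keeps the point minor.

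**The attenuation depends on the event modelled.** SAP 10.2.3 does not say whether success or failure is modelled, AVAL coding is not given, and its code lacks the DESCENDING option used in the primary-analysis code. This stands for switching unrelated to the factor, but not for related switching.

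**As-randomised may be defensible.** In protocol 3.2 the phrase about undergoing TRA follows a paragraph on allocated groups and could mean that arm. A switch prompted by a known factor is arguably an effect on TRA, and restricting to attempts conditions on an operator's decision after randomisation. This stands in part: the two populations answer different questions. It is a reason to report both, not to leave the model on the one that fits the SAP's stated outcome less well.

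**Crossovers are visible.** SAP Table 4 shows failures by crossover, stage and cause, but none of this feeds into section 10.

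**Conclusion.** The mismatch is real and follows from the text alone: the objective and outcome concern TRA as performed, while the analysis set and failure rule admit subjects in whom TRA was never tried. Its size cannot be derived from the documents. The 26% share, the attenuated ratios and the spurious 2.6 all rest on assumed switch counts, factor prevalence and effect, and the true number of switches may be zero. Severity is minor.

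Three stronger readings are not supported:

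- A reader might infer that every subject randomised to TRA enters the model. The FAS requires a recorded evaluation, so those without one drop out.
- A reader might infer that the factor estimates are bound to be attenuated. That needs switches to occur and failure to be the modelled event, if switching is unrelated to the factor.
- A reader might infer that the failure rule or as-randomised grouping is wrong in general. For the non-inferiority comparison both are coherent and should stay. The factor model compares subjects within one arm, so as-randomised grouping protects no randomised comparison there.

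**What to change.** In SAP 10.1 and 10.2.3:

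1. Define the population of the factor model as TRA-arm FAS subjects in whom a radial puncture was attempted.
2. Define the outcome as failure at protocol stages 1-4, and state which event is modelled and how AVAL is coded.
3. Report the as-randomised version alongside as a sensitivity analysis.
4. List TRA-arm subjects whose access changed before puncture separately, with reasons.

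The cost is a short SAP revision, one extra exploratory model and slightly fewer events. The eCRF is not among the documents, so it must be confirmed that it identifies pre-puncture switches and their reasons; stages 1-4 do not cover them. The primary analysis needs no change.

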**Table 7 Overview of Planned Exploratory Endpoints Analyses**

|                                                                                                                                                                                                                                                                                    | Data Displays Generated |        |         |
|------------------------------------------------------------------------------------------------------------------------------------------------------------------------------------------------------------------------------------------------------------------------------------|-------------------------|--------|---------|
|                                                                                                                                                                                                                                                                                    | Table                   | Figure | Listing |
| Association Analysis for Factors Affecting Cerebral Angiography Through TRA approach                                                                                                                                                                                        |                         |        |         |
| Descriptive statistics: 
 
the same as subgroup factors described in section 8.3
 
                                                                                                                                                    | Y                       |        | Y       |
|                                                                                                                                                                                                                                                                                    |                         |        |         |
|                                                                                                                                                                                                                                                                                    |                         |        |         |
|                                                                                                                                                                                                                                                                                    |                         |        |         |
|                                                                                                                                                                                                                                                                                    |                         |        |         |
|                                                                                                                                                                                                                                                                                    |                         |        |         |
|                                                                                                                                                                                                                                                                                    |                         |        |         |
|                                                                                                                                                                                                                                                                                    |                         |        |         |
|                                                                                                                                                                                                                                                                                    |                         |        |         |
|                                                                                                                                                                                                                                                                                    |                         |        |         |
| Generalized linear regression: risk ratio (RR) between successful and failed diagnostic cerebral angiography groups using TRA approach and its 95% CI 
 
Univariable results
 
Multivariable results with stepwise selection
 
 | Y                       |        | Y       |

